### Safety

As this is a feasibility study, data will be monitored prospectively by the research team. Any clinical concerns or complications occurring in excess of those normally experienced after this type of surgery will be reported by the Chief Investigator to the Sponsor and appropriate action taken to suspend or terminate the study until such time that patient safety can be assured in line with national guidelines for patient outcomes in surgery.

### Data management

Personal data collection during the study will be handled in accordance with Data Protection Act 1998. All information collected during the course of the trial will be kept strictly confidential.

Information will be held securely on paper and electronically at Leeds Teaching Hospitals NHS Trust and the University of Leeds Clinical Trials Research Unit (CTRU). The study site will maintain a file of essential trial documentation and will keep copies of completed case report forms (CRFs) for the trial. Completed CRFs will be sent to the CTRU for entry onto the secure trial database.

All vital signs data collected by the SensiumVitals® system are stored and retained on the hospital network. The SensiumVitals® system inherits all the hospital security procedures and data backup policies, to ensure data access and servers are secured.

In line with the principles of Good Clinical Practice guidelines, at the end of the trial, data will be securely archived for a minimum of 5 years.

### Data monitoring and validation

Day to day monitoring for completeness and quality of trial data will be conducted centrally at the CTRU by the Data Manager or their delegate. Every effort will be made to ensure that as much data as possible are available and that reasons for unobtainable data are recorded.

For a feasibility study of this nature and duration, a separate Data Monitoring and Ethics Committee is not required. The Multidisciplinary Advisory Group will meet approximately monthly and review screening, recruitment, site monitoring, data quality, protocol compliance and withdrawals.

The data manager (or their delegate) will perform verification of the forms in real time, as data are received, in accordance with the guidelines developed for the study. This will ensure that data are complete, consistent and up-to-date. Key data items will be 100% checked by the data manager or their delegate. In addition, statistical checks will be used to validate the data and check for any missing or inconsistent data.

### Progression criteria

The criteria for progression to a definitive randomised controlled trial will be as follows:The recruitment of 120 patients within 12 months who receive monitoring on the trialMissing data limited to no more than 20% attrition

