The three largest randomised controlled trials in this area show conflicting results but share common limitations. A randomised controlled trial of 402 high-risk medical and surgical patients found that continuous multi-parameter monitoring showed no effect on adverse events or mortality [9]. However, only 16% of the patients were continuously monitored for the full 72 h intended. Patient and staff compliance may have influenced the impact of the interventions. This trial was also underpowered to detect differences in clinical outcome measures given the complex nature of the intervention under investigation.

Demonstrating significant benefit over intermittent monitoring to offset the practical and economic implications of continuous monitoring is difficult and requires large, well-controlled studies in high-risk populations to demonstrate significant differences in clinical outcomes, such as critical care admissions. Given the complexity of the intervention, before a definitive trial is designed, there is the need for a feasibility study focussed not only on clinical outcome measures but also patient and nursing acceptability and compliance. Compliance is unpredictable yet crucial to the adequate assessment of the intervention. If the patient or nursing staff refuse to engage with the monitoring device, this will negate the need for a definitive trial. In addition, a feasibility study will allow the identification of barriers to recruitment and protocol adherence and allow optimisation of the trial design and the technology itself.

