### Aims

The main aim is to determine the feasibility of performing a large-scale randomised controlled trial of continuous remote monitoring after major surgery. A secondary objective is to evaluate the safety, potential efficacy and acceptability of a wearable, remote monitoring system for patients after major surgery, as compared to standard monitoring with the NEWS system alone.

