### Interventions

Patients randomised to the ‘intervention’ arm will receive a patch and standard NEWS monitoring.

When the patient comes out of theatre, they are nursed in Recovery for a short time before being admitted on to the receiving ward. The patients allocated to receive the remote monitoring will, where possible, have the patch applied in Recovery by a member of the research team. If for any reason the patch cannot be applied in Recovery, it will be applied as soon as possible upon the patient’s return to one of the participating wards. If a participant is admitted to level II/III care after surgery and before returning to a participating ward, they will have the patch applied in Recovery but the patch will only be activated once the patient returns to the participating ward. This will usually be 1–2 days later.

Two colorectal surgery wards will be participating in the study: male and female. The male ward houses 25 beds, whilst the female ward houses 28 beds.

The patch will activate on arrival on the ward, and the patient’s nurse will carry a mobile device to alert them if the vital signs stray outside of normal parameters. Remote monitoring data will also be accessible on the ward computer screens for wider access. There will be no dedicated telemetry screen for the patch data.

Nursing staff will be provided with thorough training before the commencement of the study. This will involve training in the application and removal of the patch, the use of the mobile application and how to acknowledge alerts. If the mobile devices alert the nursing staff to abnormal vital signs, the ensuing clinical response is not mandated, but left to the nurse’s discretion.

In order to monitor alarm burden, the Clinical Fellow assigned to the trial will make daily ward visits and ask the nursing staff about false alerts. The Fellow will then adjust the monitor’s delays and thresholds on an individual basis and according to clinical need, for instance, adjusting the heart rate alert threshold in patients with pre-existing cardiac arrhythmias.

During these daily ward visits, the Fellow and the research nurse will also be responsible for changing expired patches and removing patches upon patient discharge. In order to optimise patient comfort and compliance with the device, it will also be possible to adjust or replace electrodes, including after patient washing.

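### Both progression criteria can be met with very low patch wear or poor nurse engagement, which the protocol itself treats as decisive for a definitive trial

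*Protocol article*

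**What the plan says.** Progression criteria introduces its list with "The criteria for progression to a definitive randomised controlled trial will be as follows" and gives two items, run together in the extracted text: "The recruitment of 120 patients within 12 months who receive monitoring on the trialMissing data limited to no more than 20% attrition". No other progression criterion appears in the article.

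Other sections bear on the same decision:

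- Background, on engagement: "Compliance is unpredictable yet crucial to the adequate assessment of the intervention", and "If the patient or nursing staff refuse to engage with the monitoring device, this will negate the need for a definitive trial". It faults an earlier randomised trial of 402 patients because "only 16% of the patients were continuously monitored for the full 72 h intended".
- Aims: a secondary objective is to "evaluate the safety, potential efficacy and acceptability of a wearable, remote monitoring system".
- Primary outcome measures: adherence is a primary outcome. It includes the number of patients who do not wear the patch for the whole stay or for at least 5 days. No threshold is attached.
- Secondary outcome measures: patient and nurse acceptability are measured, also without a threshold.
- Data monitoring and validation: the Multidisciplinary Advisory Group meets about monthly to "review screening, recruitment, site monitoring, data quality, protocol compliance and withdrawals". No link to progression is stated.

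**The concern.** A feasibility trial exists to answer a short list of questions, and its progression criteria should be able to register a bad answer to each important one. Here the Background names lack of engagement as the finding that would remove the case for a definitive trial, and adherence is made a primary outcome. The criteria then ask only about recruitment and attrition.

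If they stay as they are, the trial could repeat the compliance problem that it criticises in the earlier trial and still satisfy every condition it set in advance. Whether low wear should stop or change the programme would then be settled after the results are known, by a team that is unblinded and has been fitting and replacing the patches.

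**Working it through.** **Inputs from the protocol article**

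- Target: 120 participants, 60 per arm (Sample size and expected accrual).
- Loss to non-participating wards: 20% (same section).
- Attrition limit: 20% (Progression criteria).
- Full-period monitoring in the earlier trial: 16% over 72 hours (Background).

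**The plan's own figures.** Number to randomise = 120 / (1 − 0.20) = 150, as stated. Number to approach = 150 / 0.5 = 300 to 150 / 0.3 = 500, also as stated. Per week over 52 weeks this is 300 / 52 = 5.8 to 500 / 52 = 9.6, which agrees with the stated 6 to 10. The accrual arithmetic is sound, and the only loss it allows for is ward destination. Patch wear does not enter it.

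**Does the first criterion register low wear?** The sample size section explains the 120 as participants with monitoring data in total. With 1:1 allocation, about 60 of them are controls on NEWS alone. No wear time is set for the other 60, so a patch patient can count after brief wear.

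**Does the second criterion register it?** Missing data are defined through the Case Report Forms and loss to follow-up (Primary outcome measures). Clinical outcome data come from records made by the usual care teams (Blinding). The modified intention-to-treat population keeps patients regardless of adherence (Planned analyses). A patient who removes the patch on the first day can therefore have complete outcome data and add nothing to attrition.

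**Illustration.** Assume 60 patch patients on participating wards and true wear of 16%:

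- Expected adherent: 0.16 × 60 = 9.6, about 10. Not adherent: about 50.
- 95% interval for a proportion of 16%: 0.16 ± 1.96 × √(0.16 × 0.84 / 60) = 0.16 ± 0.093, or about 7% to 25%.
- First criterion: 60 + 60 = 120, met if recruited within 12 months.
- Second criterion: unaffected by the 50 who did not keep the patch on.

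**Can 60 patients support a wear criterion?** At 70% observed wear, the 95% interval is 0.70 ± 1.96 × √(0.70 × 0.30 / 60) = 0.70 ± 0.116, about 58% to 82%. The exact binomial probability of reaching a go cut-off, for two cut-offs that are assumptions and not in the document, is:

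- At least 36 of 60 (60%): 0.00 at true wear 16%, 0.08 at 50%, 0.56 at 60%, 0.96 at 70%.
- At least 42 of 60 (70%): 0.00 at 16% and at 50%, 0.07 at 60%, 0.56 at 70%, 0.98 at 80%.

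The planned size separates poor from good wear well enough, and an amend band can take the cases near the cut-off.

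**The case against.** Three stronger readings are tempting, and the text supports none of them.

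- *Meeting both criteria compels a go.* The section lists criteria for progression. It does not say that they are sufficient or binding, and adherence and acceptability will be reported in any case.
- *Harm would be ignored.* Safety provides for suspension or termination if complications exceed those normally seen, and Planned analyses sends safety data to the Multidisciplinary Advisory Group at regular intervals. A suspension could itself prevent 120 patients in 12 months. What remains is narrow: the progression section does not refer to that review.
- *Ignored alerts are an unaddressed failure.* Interventions says that "the ensuing clinical response is not mandated, but left to the nurse’s discretion", so discretion is part of the design, and the Discussion plans a process evaluation of nurse engagement and alarm burden.

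Three further objections have weight. First, the Background speaks of refusal, which is not the same as partial wear; poor wear could lead to redesign and need not end the programme. That favours a three-level band over a single stop rule, but not silence. Second, the 16% comes from another trial with a 72-hour target, whereas this trial uses a wireless patch and a whole-stay or 5-day definition. The figure shows what the criteria cannot see and is no forecast. Third, the first criterion might be read as requiring patch monitoring in the patch arm. Outright refusal would then reduce the count towards 120, but early removal still would not, and the article does not state that reading.

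**Conclusion.** The point stands as a mismatch inside the protocol. The two stated criteria can both be satisfied when few patch-arm patients wear the patch as defined or when nurses do not engage with it, although the Background treats engagement as decisive and wear is a primary outcome. This is a stated rule that cannot register the protocol's own no-go condition, not detail left to a longer document.

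The illustrative size is about 10 adherent patients of 60 with both criteria met. It rests on three assumptions: 60 patch patients reach a participating ward, wear is as low as 16%, and outcome records are complete whether or not the patch is worn. The conclusion does not depend on the 16%, because no level of wear after activation enters either criterion. It is worth correcting, but it does not invalidate the trial.

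**What to change.** Amend Progression criteria, with a date, before outcome data are analysed:

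- Add a go/amend/stop band for the proportion of patch-arm patients on a participating ward who meet the wear definition in Primary outcome measures (whole stay or at least 5 days). Count a patient discharged before 5 days as adherent if the patch was worn to discharge, and reconcile this with the statement in Planned analyses that such patients are censored. The sponsor sets the cut-offs; those used above are illustrations.
- State that the first criterion counts a patch-arm patient only if the patch was activated on a participating ward.
- State that the patient and nurse acceptability results, and the safety review described under Planned analyses and Safety, are considered in the progression decision.

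No new participant procedures or extra patients are needed, since wear and acceptability are already planned outcomes. Acceptability is best taken into account without a numerical cut-off: the patient questionnaire has two rated statements and a comment box, and Planned analyses specifies thematic analysis, so a cut-off would need a new scoring rule.

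There are two costs. The trial can then fail or need amendment on compliance. And because it is already recruiting with unblinded staff on the wards, the cut-offs cannot be set in complete ignorance of how wear is going; the amendment should record what was known when they were chosen.

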### Dissemination

The trial results will be disseminated in a published manuscript and through presentation to clinical and patient and public forums with the aim of reaching healthcare workers and other stakeholders throughout the healthcare system.

## Discussion

Although continuous monitoring is routinely used in high-dependency care, it has practical implications which have to be offset in the general ward setting. Many of the existing clinical studies were limited by the complex nature of the intervention under investigation. Patient and staff compliance may have influenced the impact of the interventions. In order to ensure maximum benefit from continuous monitoring technologies, it is crucial to engage patients and nursing staff in the implementation and, ideally, development of the intervention.

Previous studies have found the main barriers to the implementation of remote monitoring are nursing engagement and alarm burden [8]. In this trial, these issues will be addressed through a concurrent process evaluation. Nurses will be provided with thorough training, and their engagement in the use of the device and perceptions of the adequacy of the training will be explored through the questionnaire and interviews. False alert rates will be monitored on a daily basis and delays and thresholds will be adjusted accordingly. Patient satisfaction will also be assessed in order to optimise the patient’s comfort and compliance with the device.

Demonstrating significant benefit over intermittent monitoring to offset the practical and economic implications of continuous monitoring requires the optimisation of the intervention to the mutual satisfaction of nursing staff and patients alike. This feasibility study will focus on not only clinical outcome measures but also patient and nursing acceptability and compliance with the intervention. This will allow the identification of barriers to recruitment and protocol adherence and allow optimisation of the definitive trial protocol.

### Trial status

At the time of submission, TRaCINg is open to recruitment.

## Appendix 1

**Table 2 Tab2:** Patient experience questionnaire

Statement	Strongly agree	Agree	Neutral	Disagree	Strongly disagree
Comfort					
The SensiumVitals® Patch was comfortable to wear.					
Quality of Care					
I felt safer because my vital signs were being monitored constantly.					
We welcome any additional comments you may have:					

## Appendix 2

**Table 3 Tab3:** Modified system usability score

	Strongly disagree				Strongly agree
I think that I would like to use this product again	1	2	3	4	5
I found the product unnecessarily complex	1	2	3	4	5
I thought the product was easy to use	1	2	3	4	5
I think that I would need the support of a technical person to be able to use this product	1	2	3	4	5
I found that the various functions in this product were well integrated	1	2	3	4	5
I thought that there was too much inconsistency in this product	1	2	3	4	5
I would imagine that most people would learn to use this product very quickly	1	2	3	4	5
I found the product very awkward to use	1	2	3	4	5
I felt very confident using the product	1	2	3	4	5
I needed to learn a lot of things before I could get going with this product	1	2	3	4	5

## Abbreviations

ASA: American society of anaesthesiologists (score for pre-operative functional status)
CTRU: Clinical Trials Research Unit
HDU: High-dependency unit
ICU: Intensive care unit
ITT: Intention-to-treat
mITT: Modified intention-to-treat
NEWS: National Early Warning Score
RCT: Randomised controlled trial
